### Minimizing missing data

In order to avoid and minimize missing data, all participants receive paper reminders with the date and time of each session. The investigator also makes phone calls to reinforce the scheduling of sessions. For data from the 24 h-VD, participants are given reminders in previous sessions so that they will not forget to complete the diary. Regarding the follow-up, the blinded evaluator contacts the participant by telephone about 3 days before the scheduled date, in order to arrange the best time and date for the assessment to be performed. As a way of monitoring adherence to treatment, the attendance records will be registries in the Session Monitoring sheets. In cases of dropout or withdrawal from the study, the data will be analyzed by intention-to-treat analysis. Participants that leave the study without performing the 12 proposed sessions (due to sickness, moving to another town, inability to attend sessions) will be considered protocol deviations.

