**Methods:**

This randomized controlled clinical trial will include 99 women, aged more than 18 years old, with urgency (score ≥ 8 in the Overactive Bladder-Validated 8-Question Awareness Tool [OAB-V8]). Women will be randomly allocated into three groups: TTNS, PTES, and placebo. The following questionnaires will be applied: the Anamnesis Record, the Incontinence Questionnaire Overactive Bladder, the King’s Health Questionnaire, the 24-Hour Voiding Diary, and the OAB-V8, at four different time points: at baseline prior to the first session, at the 6th session, the 12th session and at follow-up. The current used for the transcutaneous electrical stimulation will be a symmetrical balanced biphasic pulsed current, for 12 sessions, twice a week, for 20 minutes. Qualitative variables will be displayed as frequency and percentage, quantitative variables as mean and standard deviation. Comparison of urgency severity among groups will be performed with a repeated measures ANOVA, considering the effect of the three groups and the four evaluations, and interactions among them.

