### Sample size

The calculation of the sample size was performed in G*Power 3.1.9.2 software, considering the comparison of three independent groups (TTNS, PTES, and placebo electrostimulation) in four distinct stages (pretreatment, 6th and 12th evaluation, follow-up), an analysis of variance (ANOVA) for repeated measurements, effect size of 0.15, significance level of 5%, and 90% test power, resulting in a total of 99 participants in the study (33 participants per group).

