In the interview, the anamnesis record will be applied, which generates qualitative variables that will be presented as frequencies and percentages, and quantitative variables that will be presented as minimum value, maximum value, mean, median, standard deviation, coefficient of variation, and asymmetry coefficient. The ICIQ-OAB, KHQ, OAB-V8, and 24 h-VD will be applied, which will result in quantitative scales that will be presented as minimum value, maximum value, mean, median, standard deviation, coefficient of variation, and asymmetry coefficient.In the 6th and 12th sessions, the ICIQ-OAB, KHQ, OAB-V8, and 24 h-VD will be applied, which will result in quantitative scales that will be presented as minimum value, maximum value, mean, median, standard deviation, coefficient of variation, and coefficient of asymmetry.In the follow-up, the ICIQ-OAB, OAB-V8 and Follow-up Monitoring Card will be applied, which will result in quantitative scales that will be presented as minimum value, maximum value, mean, median, standard deviation, coefficient of variation, and coefficient of asymmetry.In all sessions during the treatment, a Session Monitoring Card will be applied that will generate quantitative variables that will be presented as minimum value, maximum value, mean, median, standard deviation, coefficient of variation, and coefficient of asymmetry.At the end of the treatment, the ANOVA for repeated measurements will be applied to verify the effects of the three groups and the three stages (pretreatment, 6th and 12th evaluation), and the interactions between them in the KHQ, ICIQ-OAB, OAB- V8, and 24 h-VD, if the residues present normality. If the residues do not present normality, a non-parametric test will be applied.At the end of the sessions and follow-up, the ANOVA for repeated measures will be applied to verify the effects of the three groups and the four stages, and the interactions between them in the OAB-V8, ICIQ-OAB, and Monitoring Cards (sessions and follow-up), if the residues present normality. If the residues do not present normality, a non-parametric test will be applied.At the end of the sessions and the follow-up, the ANOVA for repeated measurements will be applied to verify the effects of the 13 stages (12 sessions and follow-up) of the Monitoring Cards (sessions and follow-up), if the residues present normality. If the residues do not present normality, a non-parametric test will be applied.

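### Intention-to-treat is promised for dropouts, but the article names analyses that can treat incomplete women differently, and the 99 carries no dropout allowance

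*Protocol article*

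**What the plan says.** **Analysis set.** Under *Minimizing missing data*: "In cases of dropout or withdrawal from the study, the data will be analyzed by intention-to-treat analysis". The same section foresees women leaving before the 12 sessions are done, through illness, moving away or being unable to attend, and classes them as protocol deviations. It gives no expected rate.

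**Analysis.** Three places name it:
- Abstract, Methods: "Comparison of urgency severity among groups will be performed with a repeated measures ANOVA".
- *Statistical analysis plan*, main text: an ANOVA of the mixed-model type with group and time as factors, conditional on normal residuals.
- *Statistical analysis plan*, detailed list: "the ANOVA for repeated measures will be applied to verify the effects of the three groups and the four stages". This covers OAB-V8, ICIQ-OAB and the monitoring cards. The list also has a three-stage ANOVA without follow-up, and a 13-stage ANOVA for the cards (12 sessions plus follow-up). Each falls back on an unnamed non-parametric test if residuals are not normal.

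**Primary outcomes.** The outcomes section makes both OAB-V8 and the number of urgency episodes from the monitoring cards primary.

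**Size.** *Sample size* describes three groups "in four distinct stages (pretreatment, 6th and 12th evaluation, follow-up", with "effect size of 0.15, significance level of 5%, and 90% test power, resulting in a total of 99 participants". *Randomization and allocation* provides 99 paper slips. *Trial status* attributes the latest increase of three women to the sample size calculation and does not mention attrition.

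**The concern.** An intention-to-treat analysis has to say something about every randomized woman. Standard repeated measures ANOVA works on one complete row per woman, and a woman missing any stage in that analysis drops out of it entirely, including the stages she did attend. Those who leave early, for whom intention-to-treat is promised, would be the ones lost.

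Two things are at stake.
- **Bias.** If leaving is related to lack of response or to discomfort, the active-versus-placebo and TTNS-versus-PTES contrasts among completers no longer compare the randomized groups. A link to treatment is plausible: skin irritation from the stimulation is a stated criterion for discontinuing treatment.
- **Precision.** A sample size computed for complete data has no room for women removed in this way.

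**Working it through.** **1. Reproduce the 99.** Inputs from *Sample size*: k = 3 groups, m = 4 stages, effect size 0.15 (read as Cohen's f, the usual G*Power measure for ANOVA), alpha 0.05, power 0.90. The article gives neither the correlation between stages (rho) nor the sphericity correction. I assume rho = 0.5 and sphericity.

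Group-by-stage interaction, noncentral F:
- lambda = f² × N × m / (1 − rho) = 0.0225 × 99 × 4 / 0.5 = 17.82
- df1 = (k − 1)(m − 1) = 6
- df2 = (N − k)(m − 1) = 96 × 3 = 288
- power = 90.03%

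At N = 98 power is 89.7% and at N = 96 it is 88.9%, so 99 is the minimum. Under the same assumptions and in multiples of three, the within-factor test needs 81 and the between-factor test 357. Only the interaction returns 99, so these are very probably the settings used. They leave no dropout margin.

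**2. What complete-case analysis would cost.** The article gives no loss rate, so the rates below are assumptions. Same formula, with N replaced by the number complete:

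| Assumed loss | Complete | lambda | df2 | Power |
|---|---|---|---|---|
| 0% | 99 | 17.82 | 288 | 90.0% |
| 5% | 94 | 16.92 | 273 | 88.2% |
| 10% | 89 | 16.02 | 258 | 86.0% |
| 15% | 84 | 15.12 | 243 | 83.5% |
| 20% | 79 | 14.22 | 228 | 80.7% |

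**3. Dependence on the unstated correlation.** With sphericity, 99 complete women give 75.7% power at rho = 0.3 and 99.2% at rho = 0.7. The minimum N for 90% is 138 at rho = 0.3, 80 at rho = 0.6 and 61 at rho = 0.7.

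**4. How quickly complete rows disappear.** Illustration, assuming independent misses:
- OAB-V8, three post-baseline visits: 5% missed at each leaves 99 × 0.95³ ≈ 85 complete (84% power at rho = 0.5); 10% leaves 99 × 0.90³ ≈ 72 (76%).
- Monitoring cards, 13 stages: 2% missed at each leaves 99 × 0.98¹³ ≈ 76 complete; 5% leaves 99 × 0.95¹³ ≈ 51.

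The card analysis, which supplies the other primary outcome, is the more exposed. The three-stage analysis is less so, since a woman missing only follow-up stays in.

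**5. The named analyses side by side.**

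| Place | Name given | A woman missing one stage |
|---|---|---|
| Abstract | repeated measures ANOVA | excluded in the standard form |
| Statistical section, main text | mixed-model type of ANOVA | kept if a likelihood-based mixed-effects model; excluded if a mixed-design (between-within) ANOVA |
| Statistical section, detailed list | repeated measures ANOVA | excluded in the standard form |
| Same list, fallback | unnamed non-parametric test | not determined; Friedman's test, a common choice, needs complete rows |

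Nothing in the article says which of these delivers the intention-to-treat analysis.

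**The case against.** The strongest reply is that the main text of the statistical section already has the right model. A mixed-effects model fitted in R, which the article names as software, keeps women with a missing stage. The abstract and the detailed list may be shorthand for it, and *Sample size* describes only the sizing procedure. No sentence says that incomplete women are deleted, and repeated measures ANOVA after imputation would also keep them. The handling of missing stages may sit in a fuller plan.

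Much of this stands. A reader might infer that the plan certainly deletes early leavers; the article does not support that, because the mixed-model wording can be read either way. What the reply does not remove is the inconsistent naming, which is in the text and concerns the primary analysis.

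On power, a reader might infer that any loss takes power below 90%. That holds at correlation 0.5 or below with sphericity, but not above: at 0.6 about 19 women could be lost (99 − 80) and at 0.7 about 38 (99 − 61). The correlation of 0.5 is inferred from the 99; it is not an observed value. The loss rates are also mine: *Trial status* reports 52 women who completed treatment, assessments and follow-up, which is no evidence of 10% to 20% attrition.

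A reader might also fault the 99 for low power on the overall group effect or on the three-stage analysis. *Sample size* refers to a four-stage design and claims 90% for neither, so that is no error in it.

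**Conclusion.** The concern holds in a conditional form. The article promises intention-to-treat and then names analyses that can treat incomplete women differently. Following the detailed list in its standard form would break the stated analysis set for both primary outcomes, while one reading of the main text would honour it. The risk of bias depends on how many women leave and why, and the article gives no figure for either.

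The 99 is the bare minimum for the omnibus interaction, given f = 0.15 and the apparently used correlation of 0.5 with sphericity, and it contains no dropout allowance. The power loss at 10% to 15% attrition is moderate, roughly 4 to 6.5 percentage points, and rests on those assumptions and on complete-case analysis. The stronger reason to act is the unresolved choice of primary analysis. Should fix.

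**What to change.** 1. In the abstract and in both parts of *Statistical analysis plan*, name one analysis for OAB-V8 and the other repeated scores: a likelihood-based linear mixed model with group, stage (categorical) and group-by-stage, using all available scores from all randomized women.
2. For the monitoring-card urgency episodes, name a corresponding mixed model, a count model where suitable. It replaces the 13-stage complete-case ANOVA and the unnamed non-parametric fallback.
3. Add one sensitivity analysis for non-random dropout.
4. In *Sample size*, state that 99 gives 90% power for the omnibus group-by-stage interaction with all 99 women complete, state the correlation and sphericity assumptions actually used (apparently 0.5 and sphericity), and say that there is no dropout allowance. The complete-case figures above are illustrations; they should not be entered as the power of the mixed model.

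Cost: wording, a little more analysis work and a slightly less favourable power statement. No extra participants. *Trial status* says that no analysis has yet been performed, so the model could be fixed before results are seen.

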## Methods

### Trial design

This is a blinded randomized controlled trial. Outcome measures will be assessed at baseline (prior to initiation of treatment), during treatment (at the 6th session), on the last day of treatment (the 12th session), and 1 month after the completion of treatment (follow-up). Starting on March 1, 2017, participants were enrolled and randomized into three groups (TTNS, PTES, and placebo electrostimulation) by simple randomization using a 1: 1: 1 ratio. Data for the primary analysis will be collected by December 2019 and follow-up data by February 2020. Currently, no data analysis has been performed and the allocation of the groups remains blinded to the evaluator and the participants. The planning of this project followed the guidelines of the Consolidated Standards of Reporting Trials (CONSORT) and Standard Protocol items: recommendations for interventional trials (SPIRIT) guidelines.

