### Evaluation tools

After the participants sign the ICT, an investigator will apply validated questionnaires that measure the severity of the OAB (Overactive Bladder – Validated 8- Question Awareness Tool; OAB-V8) and UUI (Incontinence Questionnaire Overactive Bladder; ICIQ-OAB), and quality of life, specifically the history of urgency and urinary incontinence (King’s Health Questionnaire; KHQ). The participant will be given a 24 hour Voiding Diary (24 h-VD) (the participant will be asked to deliver the completed diary on the first day of treatment). In the 6th and 12th sessions, these four questionnaires will again be completed as a way of evaluating the course of treatment, by the same evaluator blind in relation to the groups (Table 1).

**Table 1 Tab1:** Data collection/measurement of results

	Pretreatment	1st Session	2nd Session	3rd Session	4th Session	5th Session	6th Session	7th Session	8th Session	9th Session	10th Session	12th Session	Follow-Up
Anamnesis record	+												
OAB-V8	+						+					+	+
ICIQ-OAB	+						+					+	+
KHQ	+						+					+	
24 h-VD	+						+					+	
Session Monitoring Card		+	+	+	+	+	+	+	+	+	+	+	
Follow-up Monitoring Card													*+*

*24 h-VD* 24-Hour Voiding Diary; *ICIQ-OAB* Incontinence Questionnaire Overactive Bladder; *KHQ* King’s Health Questionnaire; *OAB-V8* Overactive Bladder – Validated 8-Question Awareness Tool

The OAB-V8 is an instrument translated and validated for Portuguese [28]. It includes eight questions alluding to an initial general statement “How much have you been bothered by ...”. As options for answers, there are six variations “Never; Almost nothing; A little; Enough; A lot, and Very Much”. The score of this instrument is calculated through the sum of the questions, and can vary from 0 to 40 points; if the result is 8 or more than 8, it is indicative of OAB [28]. The ICIQ-OAB has been translated, adapted, and validated into Portuguese [29]. This is a short questionnaire with a high psychometric capacity to evaluate OAB, capable of assessing the impact of symptoms of urinary frequency, urgency, nocturia, and incontinence [30]. It consists of four basic questions: question 3a investigates urinary frequency, question 4a evaluates nocturia, and questions 5a and 6a investigate urgency and UUI, respectively. For the analysis of the results, the corresponding values of questions 3a, 4a, 5a, and 6a are added, obtaining a total of 0 to 16 points; the higher the value found, the greater the impairment [29].

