
The KHQ has been translated and validated into the Portuguese language [31]. This questionnaire is specific to UI [32]. The KHQ consists of 30 questions, divided into eight domains: general health perception, impact of UI, limitations of daily activities, physical limitations, social limitations, personal relationships, emotions, sleep/mood. The questionnaire also contains two other independent scales: one assesses the severity of UI (severity measures) and the other the presence and intensity of urinary symptoms (urinary symptom scale). The KHQ is scored in domains, so there is no overall score. The scores range from 0 to 100 and the higher the score obtained, the worse the quality of life related to that domain [31].

The 24 h-VD [3], contains data on urinary habits, and should be completed for a period of 24 hours, with information on number of urinations; amount of urine eliminated; and occurrence of urinary loss or urgency. During the study, the participant will complete the diary 3 times, referring to pretreatment, middle of treatment (6th session), and end of treatment (12th session).

During the treatment, in order to follow the micturition symptoms per session, a Session Monitoring Card will be used. This fact sheet contains open and closed questions about the urinary symptoms of the day before the session and the day of the session. It also contains a Visual Analogue Scale (VAS) [33] to indicate possible discomfort of the applied technique. The volunteer will be questioned as to their degree of discomfort during the treatment, with 0 indicating total absence and 10 the maximum level of discomfort bearable. Any side effects that the participants report will be recorded by the researcher. Over the 12 sessions, each participant will complete 12 Session Monitoring Cards, thus allowing longitudinal analysis of the voiding symptoms.

One month after completion of treatment, an investigator, blinded to the allocation of participants, will complete a Follow-up Monitoring Card. In addition to this card, the ICIQ-OAB and OAB-V8 will also be applied.

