### Measurement of results, primary and secondary outcomes

The outcome measures will be evaluated in several stages: at the beginning before the randomization (Anamnesis record, OAB-V8, ICIQ-OAB, KHQ, 24 h-VD), during the 12 sessions (Session Monitoring Card), in the 6th and 12th sessions (OAB-V8, ICIQ-OAB, KHQ, 24 h-VD), and 30 days after the end of treatment (Follow-up Monitoring Card, OAB-V8, ICIQ-OAB) (Table 1). The primary outcome of the study is urgency, measured by the OAB-V8. This was chosen as it is a validated instrument for Portuguese, with criteria defined for identification of urgency, easy to apply, objective, with robust results. It is used both as a screening tool and to raise self-identification awareness of the participant. In addition, as a primary outcome, the number of episodes of urgency will be observed (obtained in the Session Monitoring and Follow-up sheets). As secondary outcomes: voiding habits (number of diurnal urinations (Session Monitoring and Follow-up sheets and ICQ-OAB), use of absorbent pads (KHQ), urinary incontinence (number of episodes of urinary loss Session Monitoring and Follow-up sheets and ICIQ-OAB, severity of UI (ICIQ-OAB)) and quality of life (KHQ and ICIQ-OAB).

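### No 12th-session OAB-V8 or later session cards are planned for a woman who stops treatment early, and her follow-up date is ambiguous, so the late-stage intention-to-treat comparison is weaker than it need be

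*Protocol article*

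**What the plan says.** Trial design sets the post-baseline assessments "during treatment (at the 6th session), on the last day of treatment (the 12th session), and 1 month after the completion of treatment (follow-up"). Evaluation tools repeats this for OAB-V8, ICIQ-OAB, KHQ and the voiding diary: "In the 6th and 12th sessions, these four questionnaires will again be completed as a way of evaluating the course of treatment". Table 1 has the same layout, with session-numbered columns and one follow-up column. No assessment is timed from randomisation or from the first session.

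OAB-V8 is the primary outcome. The outcomes section adds a second primary measure: "the number of episodes of urgency will be observed (obtained in the Session Monitoring and Follow-up sheets"). The session cards are filled in at sessions, so this count stops when attendance stops.

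Follow-up is anchored in two ways. Evaluation tools says "One month after completion of treatment, an investigator, blinded to the allocation of participants, will complete a Follow-up Monitoring Card", which agrees with Trial design. The outcomes section says "30 days after the end of treatment (Follow-up Monitoring Card, OAB-V8, ICIQ-OAB").

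Minimizing missing data promises: "In cases of dropout or withdrawal from the study, the data will be analyzed by intention-to-treat analysis". The next sentence treats as protocol deviations "Participants that leave the study without performing the 12 proposed sessions", giving illness, relocation and being unable to get to sessions as examples. Participants and settings separately makes skin irritation a reason to stop treatment and does not say whether assessment goes on.

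**The concern.** An intention-to-treat comparison at the 12th session and at follow-up needs outcomes at those stages from women who did not finish treatment. The stated schedule does not plan a 12th-session outcome for them, and the section on minimising missing data speaks of women short of 12 sessions as having left the study. The examples it gives are reasons for not attending treatment; none is a refusal to answer a questionnaire. Its retention measures are session reminders, scheduling calls and a call before a scheduled follow-up, and none is stated to reach a woman who has stopped.

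Stopping may be related to treatment. Electrode sites and current settings differ between the active arms and placebo, and skin irritation is a stopping criterion. If reasons for stopping differ by arm, the missing late values are not a random subset. The gap arises at collection: a later analysis document can choose a model for such data but cannot supply values that were never due.

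**Working it through.** **1. What is due for a woman who stops.** The article plans four OAB-V8 stages and 13 cards (12 session, 1 follow-up). As an example, take a woman whose last session is the 7th.

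| Measure | Due as written? |
|---|---|
| OAB-V8 at baseline | yes, before randomisation |
| OAB-V8 at 6th session | yes |
| OAB-V8 at 12th session | no |
| Session cards | 7 of 12 |
| Follow-up OAB-V8, ICIQ-OAB and card | no if *completion* governs; yes if *end of treatment* means her own stopping date |

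A woman who stops before the 6th session has only her baseline OAB-V8 and the cards from sessions attended, plus follow-up on the second reading.

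**2. Timing under the second reading.** At two sessions a week, session *s* falls about *s*/2 weeks after the start: session 6 at about week 3, session 12 at about week 6. The woman who stops at session 7 would be followed up about (12 − 7)/2 = 2.5 weeks earlier after starting than a completer. The follow-up value exists but is not at the same time point, and the 12th-session value is still absent.

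**3. What the planned model can use.** The Statistical analysis plan section names a mixed-model ANOVA by group and time. Partial records can contribute to such a model, and the late-stage contrasts are then valid if values are missing at random given what was observed. That assumption is doubtful if stopping follows a reaction to treatment or lack of benefit not captured in the earlier scores.

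**4. Size, by assumption only.** The article gives no dropout rate and no outcome for stoppers. For a completers-only comparison, let *p* be the stopping rate, *c* the mean improvement in completers and *s* that in stoppers, for active (A) and placebo (P). Then

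completer difference − all-randomised difference = p_A(c_A − s_A) − p_P(c_P − s_P).

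Assume c_A = 10, c_P = 6 and s = 0 in both arms, so the completer difference is 4.0 OAB-V8 points:

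| Stopping, active / placebo | All-randomised difference | Completers differ by |
|---|---|---|
| 20% / 10% | 8.0 − 5.4 = 2.6 | +1.4 |
| 20% / 20% | 8.0 − 4.8 = 3.2 | +0.8 |
| 10% / 20% | 9.0 − 4.8 = 4.2 | −0.2 |

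If stoppers improve as much as completers in each arm, the difference is zero. Both sign and size depend on quantities that the article does not give.

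**5. Sample size, as background.** The stated 99 reproduces as the group-by-time interaction test with effect size 0.15, 5% significance, 3 groups and 4 stages, if correlation 0.5 and no sphericity correction are assumed (neither is stated). With λ = f²·N·m/(1 − ρ) = 0.0225 × 99 × 4/0.5 = 17.82 on 6 and 288 degrees of freedom, power is 0.9003; at N = 96 it is 0.8894. Under those settings 99 contains no allowance for dropout. With complete cases only, an assumed 10% loss (89 women) gives 0.860 and 20% (79 women) gives 0.807. The point made here does not depend on these figures.

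**The case against.** The strongest reply has four parts.

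- **She does have data.** A reader might infer that the intention-to-treat analysis has nothing for an early stopper. The documents do not support that: every woman has baseline questionnaires, a card for each session attended and 6th-session values if she got that far, and a mixed model can use them. This stands, and it limits the point to the late stages.
- **Follow-up may be due.** A woman whose treatment is stopped still has an end of treatment, and the follow-up call is not restricted to completers. This stands in part. Trial design and Evaluation tools say *completion*, so the article supports either reading and needs reconciling.
- **Leaving the study is not the same as stopping treatment.** The deviation sentence does not literally say that every woman who stops treatment leaves the study, and the skin-irritation rule uses different words. This is fair as to wording. But nothing in the stated schedule gives a woman who stops and stays a 12th-session assessment.
- **A condensed article may leave such procedures to a full protocol.** That would answer a complaint about a missing imputation method, which is not made here. The visit anchors, Table 1 and the status of women short of 12 sessions are stated in the article.

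A reader might also want every woman's visits moved to calendar time. Measuring after a set number of sessions is a legitimate target, and 52 women have already finished under the present timing, so that wider change is not recommended.

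**Conclusion.** The point holds as a cheap improvement. As written, no 12th-session OAB-V8 and no further session cards are planned for a woman who stops early, and her follow-up depends on which wording governs. The late-stage part of the promised intention-to-treat analysis therefore rests on missing-at-random in a setting where stopping may be related to treatment.

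No size can be put on the bias from the article. A reader might infer from an example such as the 20% / 10% row above that the effect will be overstated by about half (4.0/2.6 = 1.54). That figure needs assumed stopping rates, no improvement in any stopper and a completers-only analysis, which is not what the article describes. Equal 20% stopping gives 4.0/3.2 = 1.25, and the reversed rates give a slight understatement. The 6th-session comparison and the early cards are affected only by women who stop before those sessions.

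**What to change.** In Minimizing missing data and Table 1:

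1. Distinguish stopping treatment from withdrawing from assessment, and record sessions received and the reason for stopping.
2. For women who stop early and have not withdrawn consent, collect at least OAB-V8, ICIQ-OAB and the Monitoring Card urgency-episode count at the dates when the 6th session (about week 3), the 12th session (about week 6) and follow-up (30 days after that) would have fallen, by telephone if needed.
3. Apply this to stoppers already enrolled whose dates have not passed.
4. Reconcile *completion of treatment* (Trial design, Evaluation tools) with *end of treatment* (outcomes section).
5. Leave session-based timing unchanged for women who continue. The rule for stopping treatment is not touched.

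The cost is an amendment and a few calls by the blinded evaluator, who already telephones participants before follow-up. Some assessments would be by telephone instead of in person, and the collection rule would differ from that used for the 52 women already finished; at most 99 − 52 = 47 women could come under it.
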